MUF seeks to achieve more effective hemofiltration by hemoconcentrating the patient and reducing inflammatory mediators [12].

The surgical team at Puerta del Mar University Hospital who are taking part in the research usually use a polysulfone membrane throughout the procedure and perform high-flow continuous ultrafiltration (UF), replacing the filtered volume with Prismasol 2® pharmaceutical solution, which contains the following active substances: calcium chloride, dihydrate; magnesium chloride, hexahydrate; glucose monohydrate, lactic acid solution 90%; sodium chloride; potassium chloride and sodium hydrogen carbonate. This solution is also used for priming the CPB circuit, and it must be taken into account in the research that Prismasol 2® solution contains 3 mEq/L of lactate.

Prismasol 2® solution is used as a solution for hemofiltration in the treatment of renal insufficiency and no contraindications with CPB have been reported, since serum potassium and calcium levels are monitored every 20 minutes. The administration of sodium bicarbonate is also eliminated from priming.

Likewise, CUF during CPB is safe thanks to continuous patient monitoring throughout the procedure.

The flow rates recommended by the manufacturer for the replacement solution in hemofiltration and hemodiafiltration are as follows: Adults and adolescents: 500 - 3000 ml/hour.

The use of hemofiltration in adults during CPB procedures has evolved over the years, with studies showing the advantages of CUF or MUF in CPB procedures, such as increased hematocrit with the consequent reduction in blood transfusions, reduction of inflammatory response, improvement of hemodynamic parameters and better neurological outcomes in patients, as well as a shorter postoperative intubation time in the intensive care unit [13].

There is a disparity in the scientific literature regarding HL during and after CPB, and while Soliman R et al. [14] consider that continuous hemofiltration increases postoperative lactate levels and inotropic drug use, Kiziltepe et al. [15] describe it as a safe procedure in adult patients undergoing cardiac surgery.

Perhaps the results of the Soliman group were conditioned by the use of moderately hypothermic CPB and the use of Ringer's lactate solution at a concentration of 27.8 mEq/L for priming the CPB circuit.

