**4.4.- Specific objectives:**

- To determine plasma lactate levels in patients who undergo CPB at different stages of the process:
  - 10 minutes after starting CPB.
  - Every twenty minutes until the end of the CPB procedure
  - Twenty minutes after stopping CPB.
- To determine lactate levels in the effluent.
- To describe the behavior of variables that may influence intraoperative lactatemia levels.
- To evaluate the effects of using the polysulfone membrane continuously during the intraoperative and postoperative period.
- To describe the epidemiological profile, risk factors and surgical risk, according to the usual scores, of the patients in the study.
- To analyze the complications and side effects deriving from CPB and continuous hemofiltration with volume replacement.
- To identify patients' health status using the NANDA diagnosis classification.
- To assess patients' status of using the Nursing Outcomes Classification (NOC), before and after surgery with CPB.
- To evaluate the efficacy of the Nursing Interventions Classification (NIC), after CPB surgery using the Nursing Outcomes Classification (NOC).

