**5.4.- Description of methods:**

The proposed methods to be used in this study are based on analyses of the following instruments and variables:

- Clinical and analytical instruments.
- Record sheet of variables from the patient's medical record.
- Record sheet of intraoperative variables.
- Graph from the perfusionist and electronic data collection systems.
- Record sheet of postoperative variables.
  - Graph and records from the ICU.
  - Graph and records from the ward.
  - Lactate testing instruments.

The variables to be studied have been selected according to the existing literature regarding the factors associated with the results of the therapy used.

- Dependent variables:
  - Levels of serum lactate in mmol/L (continuous quantitative variable): at the beginning of CPB, after 10 minutes of CPB, every 20 minutes during the procedure and 20 minutes after the end of CPB.
  - Effluent lactate levels in mmol/L (continuous quantitative variable): at the end of the procedure.
  - Intra- or perioperative mortality, yes/no (dichotomous variable).
  - Complications: intubation, seizures, pleural effusion requiring drainage, yes/no (dichotomous variable).
  - Evaluation of the outcome of the intervention by the perfusionist nurse. During CPB. NOC nursing taxonomy in the preoperative period, at the end of each procedure and in the postoperative period. These outcomes consist of indicators that measure the patient's health on a Likert scale (1-5).
- Adjustment or stratification variables:
  - Predicted mortality scale (EuroSCORE[[1]](#footnote-2)).
  - Serum potassium and lactate values, immediately after surgery and with each routine blood analysis in the ICU.
- Preoperative variables:
  - Demographic variables:
    - Age: years (quantitative variable).
    - Sex: male/female (dichotomous variable).
- Biometric variables:
  - Height: centimeters (continuous variable).
  - Weight: kilograms (continuous variable).
    - The above variables will be used to calculate the body mass index (BMI): weight/height2 = kilograms/m2 (continuous variable).
- Biochemical variables:
  - Glucose: mg/dL (continuous variable).
  - Serum lactate: mmol/L (continuous variable).
  - Diagnosis upon admission: according to ICD-9 international classification.
    - Comorbidities: presence/absence in the patient's medical record (dichotomous variables):
      - Arterial hypertension.
      - Hyperlipidemia.
      - Peripheral artery disease.

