**5.7.- Statistical analysis [24]:**

- Descriptive analysis of variables: measures of central tendency and dispersion will be shown in the case of quantitative variables, while frequencies and proportions will be shown in the case of categorical variables.
- The normality of the variables will be checked using graphs and the Kolmogorov-Smirnov test.
- Homogeneity and comparability between the groups of the two arms of the study in the main confounding factors considered will be verified at the beginning of the study by means of a comparison of proportions (chi-squared test or Fisher's exact test, if necessary) and a comparison of means (Student's t-test and the Mann-Whitney U test in case of non-parametric distributions).
- The intrasubject change over time will be analyzed by comparing paired means using a t-test or Wilcoxon signed rank test (non-parametric variables), quantifying the change in each measure in relation to the baseline reference measure (first sample).
- The bivariate analysis between the CG and PG will be performed using the chi-squared test or Fisher's exact test, if necessary, and using a comparison of means (Student's t-test and Mann-Whitney U test in case of non-parametric distributions).
- In the event of non-homogeneity in any variable between the groups studied, a multivariate analysis will be performed using linear regression.

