**5.8.- Limitations of the study and ethical considerations**

The study design does not allow the use of total blinding, and the perfusionist is aware of the therapy and characteristics of the membrane at all times. According to the literature and standard practice in this country, the use of a control group should not pose any ethical dilemma if certain premises are taken into account.

The only condition that the control group must meet is that the patients must be able to manage their fluid balance by themselves, as a fluid overload has been shown to be harmful. This may mean that the patients in the control group have better renal function than those in the other group, or at least better initial diuresis. However, the primary objective is not to measure or evaluate perioperative renal function. In addition, a hemofilter will be available for use if control patients are not able to manage their fluid balance through diuresis. Finally, if surgery times are shorter in the control group, the lactatemia levels may be lower than in the other group with a longer duration. If this is the case, we will stratify the treatment groups by selecting cases with a shorter duration. In any case, a minimum time of 60 minutes is established from start of CPB + CUF and to the end of CPB.

It will be carried out according to the international ethical recommendations (the Declaration of Helsinki and the Oviedo Convention), since the use of the best available therapy according to the patients' circumstances is contemplated at all times.

In order to safeguard confidentiality, all personal data collected as part of this study will be treated in accordance with Organic Law 15/1999, of December 13, on personal data protection.

Likewise, informed consent will be requested for surgery that includes the usual CPB procedures with or without hemofiltration.

Informed consent will also be requested for use of any data deriving from medical records and analytical determinations. Access to personal information will be restricted to the investigator and authorized personnel and all of them will be obliged to maintain confidentiality. If the work is published, the patients' identity will remain anonymous at all times.

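### Section 5.7 measures lactate change from an undated first sample, which 4.4 places 10 minutes into bypass and 5.4 at its start

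*Protocol*

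**What the plan says.** Section 5.7 tests within-patient change with a paired t-test or Wilcoxon test, "quantifying the change in each measure in relation to the baseline reference measure (first sample"). It does not say when that sample is drawn. Three places in the protocol could supply it:

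- Section 4.4 begins the plasma lactate series with "10 minutes after starting CPB" and lists nothing earlier.
- Section 5.4, under dependent variables, sets serum lactate "at the beginning of CPB, after 10 minutes of CPB, every 20 minutes during the procedure and 20 minutes after the end of CPB". Here the 10-minute sample is the second.
- Section 5.4 also lists "Serum lactate: mmol/L (continuous variable") among the biochemical variables that follow the preoperative heading, again without a time.

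On filtration, section 3 says that the team "usually use a polysulfone membrane throughout the procedure and perform high-flow continuous ultrafiltration (UF"). Section 5.8 says that "a minimum time of 60 minutes is established from start of CPB + CUF and to the end of CPB". Section 3 says of the replacement fluid that "This solution is also used for priming the CPB circuit" and that "Prismasol 2® solution contains 3 mEq/L of lactate".

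The comparison between arms is a separate item in 5.7. It names the tests but does not say whether they apply to levels or to changes. Section 5.1 frames the comparison as lactate clearance, a quantity per unit of time.

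**The concern.** A baseline should precede the treatment whose effect is measured from it. Lowering intraoperative lactate is the first hypothesis (4.2) and the first general objective (4.3). The stated rule, read with 4.4, gives a reference drawn after bypass has begun and, in the filter arm, probably after filtration has begun. Read with 5.4, it gives a reference that can be free of treatment. At stake are a change value that depends on which section the analyst follows, a choice that could be made after the data are seen, and, under 4.4, loss of the early part of the effect.

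**Working it through.** **1. The plan's own figures.** No power calculation is given, so there is none to reproduce. The only check available is 8 blocks × 5 patients = 40 (5.1), which agrees with about 40 patients (5.6).

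**2. The two schedules.** Every sample in 4.4 also appears in 5.4. The start-of-CPB sample appears only in 5.4. So the first sample is at 10 minutes under 4.4 and at 0 minutes under 5.4.

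**3. Effect on one patient's change.** With L(t) the lactate at t minutes, change is L(t) − L(10) under 4.4 and L(t) − L(0) under 5.4. At every later time the two differ by L(10) − L(0).

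Prime mixing alone gives an idea of the size. Assumed, not in the protocol: prime V = 1.0 to 1.5 L, prior lactate 0.8 to 1.5 mmol/L, 14 L of extracellular fluid mixed by 10 minutes. The 3 mEq/L is from section 3.

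- L(10) = (14 × prior + 3V)/(14 + V) = 0.95 to 1.65 mmol/L.
- If L(0) is drawn before any mixing, L(10) − L(0) is +0.10 to +0.21.
- If L(0) is drawn once the prime has mixed with an assumed 3 L of plasma, L(0) = (3 × prior + 3V)/(3 + V) = 1.35 to 2.00, and L(10) − L(0) is −0.28 to −0.52.

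Even the sign depends on the exact moment of the first draw. This calculation has no term for treatment arm, so it shows that the change value is undefined. It does not show bias between arms.

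**4. Effect on the difference between arms.** Let D(t) be the expected difference at t minutes, with D(0) = 0 by randomization. Change from L(10) estimates D(T) − D(10) = D(T) × (1 − f), where f = D(10)/D(T). If the effect builds linearly, f = 10/T. The 60 minutes is the minimum in 5.8; the other durations are assumed.

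For scale, assume 20 patients per arm, two-sided alpha 0.05 and an SD of change of 1. The standardized difference with 80% power is (1.960 + 0.842) × √(2/20) = 0.886. Multiplying it by 1 − f gives:

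| CPB time T (min) | Share lost, 10/T | Remaining difference | Power | Per arm for 80% |
|---|---|---|---|---|
| 60 | 16.7% | 0.738 | 0.65 | 29 |
| 90 | 11.1% | 0.788 | 0.70 | 26 |
| 120 | 8.3% | 0.812 | 0.73 | 24 |
| 180 | 5.6% | 0.837 | 0.75 | 23 |

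If the effect builds early, f = (1 − exp(−10/τ))/(1 − exp(−T/τ)). With assumed τ of 20 to 40 minutes and T of 60 to 180 minutes, the loss is 22% to 41% and power is 0.38 to 0.59.

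**5. Is linear build-up reasonable?** The glossary (Annex IV) defines high flow as at least 35 ml/kg/h. For an assumed 70 kg that is 2,450 ml/h, or about 408 ml in 10 minutes. In a well-mixed pool of V liters, the fraction exchanged by t hours is 1 − exp(−2.45t/V). For assumed pools of 5, 15 and 35 L it is 0.0784, 0.0269 and 0.0116 at 10 minutes, against 0.3874, 0.1507 and 0.0676 at 60 minutes. The ratios are 20%, 18% and 17%. Steady removal is thus close to the linear case at 60 minutes. The 22% to 41% losses would need a faster mechanism.

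**The case against.** The strongest reply is that 5.4 is where variables are defined and 4.4 is only a list of objectives. On that view the first CPB sample is the one at the start of CPB, and the 10-minute baseline arises only if 4.4 is read alone. This is a fair reading, but 5.7 does not point to 5.4, and 4.4 sets out its own timed schedule.

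A reader might infer that the baseline contains treatment effect whichever section is followed. The documents do not support that. The 5.4 sample can be drawn at time zero with essentially no filter effect. The start of filtration is also inferred: section 3 describes usual practice, 5.8 sets a minimum duration, and 5.4 records hemofiltration time separately from support time.

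A reader might also infer that the main comparison of arms is biased. The sentence in 5.7 governs the paired analysis. The between-arm item does not mention change, and if levels are compared the baseline does not enter. The clearance wording in 5.1 suggests a starting value without settling the matter.

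Nor does the lactate in the prime show bias: with the same prime, both arms shift alike.

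Finally, a statistical analysis plan may define the baseline, and leaving that detail to it is normal. Here, though, the protocol states a rule itself, and its own two schedules give that rule different answers.

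**Conclusion.** The concern holds in limited form. It is certain that the reference in 5.7 is undated and that 4.4 and 5.4 yield different first samples. It is conditional that the reference is post-treatment: this needs 4.4 to be followed and filtration to start with CPB. It is further conditional that the comparison of arms suffers: this needs change or clearance to be compared. If all these hold, the difference is attenuated by about 17% at 60 minutes, falling to about 6% at 180 minutes, under linear build-up, and by more if the effect comes early.

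The attenuation is toward no difference, provided that the early effect has the same sign as the later one. The power figures are illustrative only. They assume an even split of 40 patients and an SD of change that is the same for both baselines. This should be fixed before analysis, but it does not invalidate the design.

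**What to change.** - In 5.7, replace the undated first sample with one named reference drawn before CPB flow and filtration in both arms. Either the 5.4 start-of-CPB sample, fixed at time zero before flow, or the preoperative lactate with its time stated would serve.
- Add that sample to 4.4 so that its schedule matches 5.4.
- State that the 10-minute sample is post-baseline.
- Use the named baseline in any comparison of arms on change or clearance, preferably as a covariate.

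The cost is protocol wording, since both candidate samples are already listed in 5.4. The time-zero sample does need its moment of drawing specified. The preoperative value has a drawback: change from it also includes induction, surgery before CPB and the prime, which add variation unrelated to filtration. It is therefore not clearly better than a time-zero sample.

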**5.- Methodology**

**5.1.- Study design**

A randomized, patient- and data analyst-blinded clinical trial to compare outcomes in terms of the lactate clearance rates (quantity/unit of time) of the assigned therapy groups. Two treatment groups will be established: one control group without hemofiltration (CG or 1), one group with hemofiltration using a polysulfone filter (PG or 2).

To ensure an unbiased assessment of treatments, randomization will be performed in eight blocks of five patients. The study groups will be equivalent in all aspects except the procedures they undergo.

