**5.5.2.- Exclusion criteria:**

- Patients who do not sign the informed consent form.
- Emergency medical condition in which it is not possible to collect study data.
- Heart condition requiring the use of hypothermia or hyperthermia during CPB.
- Patients without a minimum time of 60 minutes before decannulation (after the end of myocardial reperfusion, unclamping of the aorta and the end of CPB).
- Patients who cannot manage their fluid balance on their own through diuresis prior to CPB.
- Patients who are unable to manage excess volume during the surgical procedure by means of spontaneous or forced diuresis with diuretics (positive cumulative balance despite intravenous bolus of diuretics after 75% of the anticipated duration of CPB according to the course of the surgery).

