**5.6.- Sample size**

The sample size will result from the prospective inclusion of a consecutive series of patients over 10 months who undergo surgery with CPB by the investigator in the Cardiovascular Surgery Unit of Puerta del Mar University Hospital, Cádiz, under normothermic conditions. As a preliminary analysis, this cohort is estimated to consist of about 40 patients in the Cardiovascular Surgery Unit.

The study population will comprise a sample of patients who meet the inclusion criteria between February 2017 and December 2017.

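### Section 5.7 names Student's t-test for the between-arm comparison of means with no provision for unequal spread, while equal arm sizes are not assured; specifying Welch's test is a minor, nearly free improvement

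*Protocol*

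**What the plan says.** All references are to the protocol.

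- **Test.** For continuous outcomes, section 5.7 plans a "comparison of means (Student's t-test and Mann-Whitney U test in case of non-parametric distributions").
- **Rule for choosing.** Section 5.7 states: "The normality of the variables will be checked using graphs and the Kolmogorov-Smirnov test". Equality of variances is not mentioned, and no unequal-variance version of the t-test is named.
- **Allocation.** Section 5.1 says "Two treatment groups will be established" and that "randomization will be performed in eight blocks of five patients". It gives neither an allocation ratio nor the make-up of a block.
- **Size.** Section 5.6 says "this cohort is estimated to consist of about 40 patients".
- **Outcome.** Section 5.4 lists "Levels of serum lactate in mmol/L (continuous quantitative variable") at the start of bypass, at 10 minutes, every 20 minutes during the procedure and 20 minutes after bypass. No SD is given for either arm.
- **Later changes to the analysed numbers.** One exclusion in 5.5.2 is judged "after 75% of the anticipated duration of CPB according to the course of the surgery". Section 5.8 allows the groups to be restricted to shorter cases if surgery turns out shorter in the control arm. It also expects that controls may have better renal function.

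The protocol states no significance level and plans no confidence intervals.

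**The concern.** The pooled t-test keeps its level if the two arms have the same spread, and nearly keeps it if they have the same size. When both differ, the pooled variance is weighted towards the larger arm, and the standard error is too small or too large depending on which arm is more variable. The plan does not ensure equal sizes, and its rule for choosing a test does not look at spread.

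Three features can unbalance the analysed arms: the odd block size, exclusion or selection after allocation, and serial samples whose later time points include only patients still on bypass. What is at stake is whether p-values from the t-test branch mean what they appear to mean. The distortion can go either way, towards too many false positives or towards an over-cautious test.

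**Working it through.** **Inputs from the protocol.** Eight blocks of five and two arms (5.1); about 40 patients (5.6); Student's t-test if the data look normal (5.7).

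**Assumptions, because the protocol gives no figure.** Two-sided 5%; SD ratio between arms from 1 to 3, in either direction; each block split 3:2 or 2:3; normal data with equal means.

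**Step 1: the plan's own figure.** 8 × 5 = 40, which agrees with 5.6. This is only an arithmetic match, since 40 is an accrual estimate and not a power calculation.

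**Step 2: reachable splits.** A block of five cannot be divided equally between two arms.
- If the same arm receives three in every block, the totals are 8 × 3 = 24 and 8 × 2 = 16.
- If the larger share is drawn at random per block, one arm's size is 16 + Binomial(8, ½). Then P(24:16 in either direction) = 2 × 1/256 = 0.8%. P(18:22 to 22:18) = (28 + 56 + 70 + 56 + 28)/256 = 238/256 = 93%.

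**Step 3: why a pooled test goes wrong.** Let n₁, s₁ belong to the larger arm and n₂, s₂ to the smaller.
- Pooled variance: [(n₁−1)s₁² + (n₂−1)s₂²]/(n₁+n₂−2).
- Variance the test uses: pooled variance × (1/n₁ + 1/n₂).
- True variance of the difference: s₁²/n₁ + s₂²/n₂.

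At 24:16 with SD ratio 2:
- *Smaller arm more variable.* Pooled (23×1 + 15×4)/38 = 2.184. The test uses 2.184 × 0.1042 = 0.228, and the truth is 1/24 + 4/16 = 0.292. The true standard error is √(0.292/0.228) ≈ 1.13 times the one used, so the test rejects too often.
- *Larger arm more variable.* Pooled (23×4 + 15×1)/38 = 2.816. The test uses 0.293, and the truth is 4/24 + 1/16 = 0.229. The true standard error is about 0.88 times the one used, so the test rejects too seldom.

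At 20:20 the two variances are the same in expectation (0.25 and 0.25).

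**Step 4: simulated error rate** (200,000 data sets per setting).

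| Split | SD ratio | Student, smaller arm more variable | Student, larger arm more variable | Welch |
|---|---|---|---|---|
| 24:16 | 1 | 5.0% | 5.0% | 5.0% |
| 24:16 | 1.5 | 7.0% | 3.5% | 4.9-5.0% |
| 24:16 | 2 | 8.5% | 2.9% | 5.0% |
| 24:16 | 3 | 10.1% | 2.4% | 5.0% |
| 22:18 | 2 | 6.8% | 4.0% | 5.0-5.1% |
| 21:19 | 2 | 6.0% | 4.6% | 5.0-5.1% |
| 20:20 | 2 | 5.2-5.3% | (same) | 4.9-5.1% |

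Averaged over random block orientation, Student gives 5.1% (SD ratio 1.5), 5.3% (2) and 5.6% (3); Welch gives 5.0%.

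**Step 5: the Mann-Whitney branch.** At 24:16 and SD ratio 2 it gives 7.4% (smaller arm more variable) or 4.2% (larger arm more variable). The fallback named in 5.7 therefore does not remove the problem, and changing the t-test does not repair the fallback.

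**Step 6: cost of Welch when the SDs are equal** (200,000 data sets per setting). At 24:16, power for a difference of 0.8, 0.9 and 1.0 SD is 67.7%, 77.5% and 85.6% with Student, against 67.2%, 77.0% and 85.2% with Welch. The loss is about 0.5 points. At 20:20 it is about 0.1 points.

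**The case against.** The other side has five arguments.

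1. **Pooling is not written down.** Section 5.7 does not say equal-variance or pooled, and the version of a t-test is a detail that a statistical analysis plan might settle. This stands in part. However, the protocol names a specific test whose ordinary meaning is the pooled one, and it fixes normality as the only switch. That is a choice made, not a blank left.

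2. **The 24:16 split is a worst case.** A reader might infer from eight blocks of five that the trial will end up 24:16. The protocol does not support that, because it gives no block make-up. If the larger share is drawn at random per block, that split has 0.8% probability and the average error is close to nominal. This stands fully.

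3. **The unequal spread is hypothetical.** No SD appears in the protocol. If the filter did nothing and the arms stayed exchangeable, the distributions would be identical and the pooled test would keep its level. If the filter lowers both mean and spread, a false-positive rate is not the issue. This stands for a clean randomised comparison. It is weaker here, because exclusion during bypass, selection by duration and the expected difference in renal function can make the analysed arms differ without any filter effect. Such selection could also bias the means, which no choice of t-test repairs.

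4. **Skewed lactate may go to Mann-Whitney.** True, and that limits the benefit to variables that pass the normality check.

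5. **Unequal numbers at later samples are possible, not established.** Also true. Sections 4.4 and 5.4 give only the sampling schedule.

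**Conclusion.** The point holds as a minor, conditional improvement. The test named in 5.7 is sensitive to unequal spread when arm sizes differ, the plan does not assure equal sizes, and a test without that weakness is available at almost no cost.

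The effect depends on how far size and spread differ together. At SD ratio 2 it is about 3.5 percentage points upward or 2 downward at 24:16, about 2 up or 1 down at 22:18, and next to nothing at 20:20 or on average over random block orientation. These figures rest on an assumed two-sided 5% level, assumed SD ratios, normal data and 3:2 blocks. Exclusions after allocation could take the split beyond 24:16, so that is not a strict bound.

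Two stronger readings should be resisted. One is that the trial's p-values are wrong; the protocol gives no evidence that the spreads differ. The other is that a stated 5% level or planned confidence intervals are breached; the protocol states no level and plans no intervals. The point would apply to any interval computed from the pooled variance, should one be reported.

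**What to change.** In 5.7, specify Welch's (unequal-variance) t-test wherever Student's t-test is named for a between-arm comparison of means. The paired t-test for change within a patient is not affected.

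The cost is a change of wording and, when the SDs are equal, about 0.5 points of power or less. No extra data or patients are needed.

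The change leaves the Mann-Whitney branch as it is, so a significant result there should not be read as a pure difference in location if the spreads clearly differ. Stating the block make-up in 5.1, or using even blocks, would remove the planned part of the imbalance. It would not remove the part that comes from exclusions, case selection or serial sampling, so the wording in 5.7 is worth changing in any case.

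### Covariate adjustment in 5.7 depends on an observed imbalance, so the preoperative lactate already collected has no assured place in the between-arm lactate comparison

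*Protocol*

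**What the plan says.** Three statements in protocol section 5.7 together set the analysis.

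- Comparability is checked by testing one arm against the other: "Homogeneity and comparability between the groups of the two arms of the study in the main confounding factors considered will be verified". The tools are chi-squared or Fisher tests for proportions, and t or Mann-Whitney tests for quantitative variables.
- The default comparison is unadjusted: "The bivariate analysis between the CG and PG will be performed using the chi-squared test or Fisher's exact test, if necessary", with the t-test or Mann-Whitney test for quantitative outcomes.
- Regression is conditional: "In the event of non-homogeneity in any variable between the groups studied, a multivariate analysis will be performed using linear regression". No threshold for non-homogeneity, covariate list or model is given.

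Section 5.4 lists lactate among the preoperative biochemical variables: "Serum lactate: mmol/L (continuous variable". The outcome is the serial measurement during the operation: "Levels of serum lactate in mmol/L (continuous quantitative variable): at the beginning of CPB", then at later times on and after bypass. Section 5.4 also has a heading "Adjustment or stratification variables". Under it stand EuroSCORE and the potassium and lactate values taken after surgery and in the ICU. Preoperative lactate is not there, and 5.7 gives none of the listed variables an unconditional role.

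**The concern.** When allocation is random, a between-arm difference in a baseline variable is a chance event. Its size does not show whether the variable predicts lactate. A rule that adjusts when a difference is seen will therefore take up variables that differ by accident and usually pass over a strong predictor that happens to be balanced. Adjustment earns its precision from the correlation between covariate and outcome, and that gain is available whether or not the arms differ.

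Two things make this matter here. The trial expects about 40 patients, so precision is scarce. And the trigger covers any variable, which leaves room for variables measured after randomisation, such as bypass time or the postoperative lactate in the 5.4 adjustment list. Treatment may affect these, and conditioning on them can remove part of the effect being estimated.

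This is not a detail left to a later analysis plan. The protocol itself states the conditional rule.

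**Working it through.** **Inputs from the protocol.** About 40 patients (5.6), matching eight blocks of five (5.1): 8 × 5 = 40. The forecast is of recruitment. No effect, SD, alpha or power is stated, so there is no power figure to reproduce.

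**Assumptions, none of them in the documents.** 20 per arm (the ratio is not stated, and a block of five cannot split evenly, so 16/24 was also run); two-sided 5% for baseline and outcome tests; true effect 0.8 SD; Normal data; correlation ρ between preoperative and intraoperative lactate of 0, 0.3, 0.5 or 0.7. The trigger is read as a baseline t-test on preoperative lactate with p < 0.05.

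**Step 1, formula.** Adjustment reduces the residual SD from 1 to √(1 − ρ²). Approximate power is Φ(0.8 / (SD × √(2/20)) − 1.96).

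- Unadjusted: 0.8 / 0.3162 = 2.530; Φ(0.570) = 71.6%.
- ρ = 0.3, SD 0.954: Φ(0.692) = 75.6%.
- ρ = 0.5, SD 0.866: Φ(0.961) = 83.2%.
- ρ = 0.7, SD 0.714: Φ(1.582) = 94.3%.

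The t distribution with 37 or 38 degrees of freedom lowers these by about 2 to 3 points, so the comparison below is simulated.

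**Step 2, simulation (100,000 trials per row).**

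| ρ | Unadjusted power | Trigger rule power | Always adjusted power | Always minus trigger | Type I error, trigger rule |
|---|---|---|---|---|---|
| 0 | 69.6% | 69.3% | 68.4% | −0.9 | 4.9% |
| 0.3 | 69.3% | 69.3% | 72.1% | +2.8 | 4.9% |
| 0.5 | 69.3% | 70.0% | 80.0% | +10.0 | 4.4% |
| 0.7 | 69.0% | 70.7% | 92.5% | +21.8 | 3.6% |

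The rule recovers almost none of the gain because the baseline lactate test is significant in only about 5% of randomised trials. With 16/24 allocation and ρ = 0.5, power is 68.5% under the rule and 78.8% with adjustment always. In terms of sample size, 40 / (1 − ρ²) gives 44, 53 and 78 unadjusted patients at ρ = 0.3, 0.5 and 0.7.

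**Step 3, a wider trigger.** Suppose imbalance in any of k independent variables brought in a model that also contained preoperative lactate. The chance of triggering is 1 − 0.95^k: 22.6%, 40.1% and 64.2% for k = 5, 10 and 20. Weighting the unadjusted and adjusted powers by that chance, and ignoring the cost of extra covariates:

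- ρ = 0.5: 0.226 × 80.0 + 0.774 × 69.3 = 71.7%; likewise 73.6% and 76.1%. The remaining loss is about 8, 6 and 4 points.
- ρ = 0.7: 74.3%, 78.4% and 84.1%. The remaining loss is about 18, 14 and 8 points.

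The protocol does not say how many variables are tested or which enter the model, so neither step is the definitive reading.

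**The case against.** **The size is not established.** The correlation is unknown. Section 5.4 does not say when the preoperative lactate is drawn, and it precedes haemodilution with a prime that itself contains lactate (section 3), so a high correlation cannot be presumed. At 0.3 the gain is about 3 points and at zero there is a small loss. The power figures also depend on a narrow reading of the trigger. All of this stands, and the figures are illustrations only.

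**Imbalance may not be pure chance here.** Section 5.8 anticipates better renal function or diuresis among controls, and 5.5.2 excludes patients on fluid balance observed during bypass. Describing comparability is therefore useful. But a significance test in 40 patients is a weak detector of such selection, and adjusting for whatever it flags does not repair post-randomisation exclusions. This supports the descriptive table, not the trigger.

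**Significance is inferred.** No threshold is stated, and regression might supplement the unadjusted test instead of replacing it. That is fair. Yet hypothesis tests are the only check of homogeneity described, and either way the model remains undecided until the data are seen.

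**Stronger readings to set aside.**

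- A reader might infer that the baseline is taken after treatment starts and so subtracts part of the between-arm effect, because 5.7 speaks of "quantifying the change in each measure in relation to the baseline reference measure (first sample" and the list in 4.4 opens with "10 minutes after starting CPB". The documents do not support this. That reference is given only for the within-patient paired analysis, the between-arm comparison subtracts no baseline, and 5.4 lists a sample at the start of bypass.
- A reader might infer that the rule inflates type I error. In the form simulated it does the reverse. Only if the open wording let the more favourable of the two analyses be picked would the error rise, to 6.5%, 7.4% and 8.2% at ρ = 0.3, 0.5 and 0.7. The protocol does not plan that.
- Nothing in the documents shows that EuroSCORE, a mortality score, predicts lactate. Its case as a covariate rests only on its label in 5.4.

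**Conclusion.** The point holds. Section 5.7 makes adjustment conditional on an observed difference, does not restrict the trigger to pre-randomisation variables, and gives the preoperative lactate no assured role. The analysis is not invalid. It is inefficient and its model is not fixed in advance.

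At 20 per arm, 0.8 SD, two-sided 5% and a trigger on preoperative lactate alone, the loss of power is about 3, 10 and 22 points at correlations of 0.3, 0.5 and 0.7. It is less if other imbalances also bring lactate into the model. At zero correlation, always adjusting costs about 1 point. The direction is secure for any moderate correlation. The size is not known from the documents.

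**What to change.** In section 5.7:

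1. Delete the sentence that makes regression depend on non-homogeneity, and replace the baseline significance tests with a descriptive table by arm.
2. State that the between-arm comparison of serum lactate always uses a linear model with arm and preoperative serum lactate, whatever the baseline table shows. EuroSCORE may be added as a second fixed covariate, since 5.4 already labels it for adjustment.
3. State that no variable measured after randomisation enters as a covariate, and remove the postoperative potassium and lactate from the adjustment list in 5.4.
4. State in 5.4 when the preoperative lactate is drawn, so that the covariate is clearly a pre-treatment value.

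The preoperative lactate and EuroSCORE are already collected, so the cost is wording, one degree of freedom per covariate, and about 1 point of power if preoperative lactate turns out to be unrelated to the outcome.
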